### Process data collection

In addition to data gathered from interviews and SHP electronic questionnaire, a range of process data will be gathered through other mechanisms to capture additional context and individual-level information that might influence the study outcomes. Project supervisors and project managers will maintain a diary to gather information about the different activities, events or interventions by the government or other agencies in the study sites that can influence the study outcomes. In addition to this health system level data, the field team will also collect and record individual level information about the participants which is not captured by the SHP application; for example, any special diet taken by the women to improve their blood haemoglobin during, after pregnancy or details of treatment received during pregnancy or postpartum due to maternal or child complication, any socio-economic factor that can influence the general well-being of the women participating in the study.

### Mixed methods data collection for process and implementation evaluation

#### To assess whether the SHP study has been implemented as planned (implementation fidelity, dose)

To assess whether, and to what extent, the study has been implemented as intended, we will assess fidelity and dose (number of visits) of the trial procedures themselves. This will be collected using process data records, including frequency of training, completion of electronic case record files, and activity logs, drawing on SHP app-based data sources described above. Explain whether, how, and why the intervention has been effective (Reach, Effectiveness, Adoption, Acceptability, Implementation, Maintenance).

We will collect effectiveness and implementation outcomes.

Effectiveness outcomes: This will be based on the primary and secondary outcomes of the SHP trial.^
26
^Implementation outcomes: This will be assessed using the RE-AIM framework and Proctor et al.’s typology. Reach will assess the potential reach of the SHP intervention, that is, whether it is used in all eligible participants (proportion of the target population and its representativeness). Effectiveness will assess the impact on health outcomes, including positive, negative, and unintended consequences. Adoption will assess how well and to what extent the intervention has been taken up by the participants of the SHP trial (including how representative this is for the target population in the setting). Implementation will explore the extent to which each of the SHP components were implemented and/or adapted, including an assessment of the costs of delivery. Maintenance will assess the degree to which SHP was sustained at both setting level (in sites) and individual level (among participants). Acceptability will assess to what degree the intervention was acceptable for the participants of the trial (women, ASHAs, primary care doctors). Feasibility will assess to what extent the SHP intervention can be adopted, implemented, and sustained as intended. To assess this, a range of data will be used, including trial data, checklists, surveys, and costing and administrative data, with app-based process data drawn from the SHP platform as described above. Topic guides for qualitative interviews and focus groups will be informed by the process evaluation framework, Proctors’ framework^
34
^ and Weiner’s Implementation Measures,^
43
^ translated into local languages, and piloted before administration.

#### Examine how barriers, facilitators, and applied strategies affected the implementation of the intervention

To understand the impact of barriers, facilitators, and applied strategies on the implementation process, qualitative methods (interviews, FGDs and surveys) will be conducted during and after the implementation of the study. The data collection will explore perceptions of barriers and facilitators of the intervention, by women, ASHAs, ANMs, primary care doctors, district officials, and study team. In addition, data from the process evaluation framework on maintenance and sustainability (see above) will feed into the analysis.

Throughout the trial implementation and evaluation process, we will incorporate feedback loops to assess the effectiveness of the strategies, and to improve the quality of the process implementation. Regular quantitative and qualitative monitoring data from field supervisor reports/notes, logistics chain surveillance, and mid-line assessments, together with SHP app-based monitoring data described above will be triangulated and revised. Additional intervention strategies will be defined by the operations group and the delivery team to ensure implementation success.

#### Understand what and how contextual factors and mechanisms impacted the outcomes

The realist evaluation approach will be used to understand contextual factors and mechanisms that contributed to the implementation and outcomes. As defined by the realist approach, in order to analyse the effectiveness of an intervention, it is essential to understand mechanisms (M) and the contexts in which they operate (C) and how they affect an outcome (O) (C + M = O).^
31
^ Assumed mechanisms will be tested and refined through both quantitative data and qualitative insights from interviews and FGDs. Stakeholder input will be essential in developing these configurations and refining the programme theory.

#### Understand what might be required for SHP to be sustained and widely implemented in similar clinical settings (sustainability)

Qualitative interviews and FGDs will be conducted during and after the implementation of the study to better understand what may be required to sustain the intervention. The data collection will explore perceptions of the intervention, and any barriers or opportunities to wider implementation by women, ASHAs, ANMs, primary care doctors, district officials, and study team. In addition, perspectives of decision-makers in government will be consulted to explore financial and technical sustainability and policy implementation, including early insights to integration to existing platforms or other opportunities moving from project to programme which would be fully run and administered by the local authority. In order to understand the extent to which the intervention can be maintained and continued within an ongoing service setting, including its durability, we will administer the Program Sustainability Assessment Tool^
51
^ with women, ASHAs, ANMs, primary care doctors, district officials, and study team after completion of the trial.

### Data analysis

The process evaluation will be analysed using a mixed methods approach. The analysis will aim to seek possible explanations for implementation and process outcomes achieved in the SHP trial.

Quantitative and qualitative data will be triangulated and reported together to provide a holistic understanding of the implementation process and outcomes. Data from multiple stakeholders namely women, ASHAs, ANMs, primary care doctors, district officials, and study team will be triangulated to ensure that multiple perspectives are captured. The process evaluation framework (Figure 2) will guide the data analysis for process evaluation data. This framework will ensure that all aspects of the intervention, context, mechanisms, and outcomes are analysed comprehensively.

The quantitative data will be analysed as part of the overall SHP trial statistical analysis plan and will be published online before the SHP database will be locked. Contextual variables captured through process data (e.g. health system factors, implementation intensity, site-level characteristics, and participant socio-demographic factors) will be operationalised as covariates or stratification variables in the quantitative analysis. Where appropriate, multivariable regression models and subgroup analyses will be used to assess the influence of contextual factors on primary and secondary outcomes. Qualitative exploration through interviews and FGDs will inform interpretation of all major process and implementation themes.

Qualitative data analysis will be done in several stages, using a mixed deductive and inductive thematic analysis.^
45
^ Audio recorded data from interviews and FGDs will be translated and transcribed in English. Thematic analysis of the data will be conducted using Atlas.ti software. Coding will be conducted by two trained qualitative researchers from the study team. An initial subset of transcripts will be independently coded to develop and refine the coding framework. Inter-coder agreement will be discussed and discrepancies resolved through consensus, with iterative refinement of the codebook before coding of the full dataset. Data will be coded using the constructs of the process evaluation framework (Figure 2, above). A combination of deductive and inductive coding will allow for generation of new themes outside these frameworks. Themes will be generated, and subsequently common and distinctive key themes and constructs will be identified based on frequency (e.g. elicited in >60% participants) and expressed relevance of participant groups (patients, healthcare workers, primary care doctors, field staff). The themes and findings will be triangulated with findings from observations, patient journey mapping, surveys, notes from field staff and SHP app data, and other information. Reporting of qualitative data will follow the COREQ guidelines.^
52
^ To investigate the influence of context and mechanisms on outcomes, the findings from the CMO configurations will be analysed using thematic analysis using Atlas.ti, descriptive statistics, and multivariate analysis of variance to assess differences in mechanisms. Figure 4 outlines the flow of data collection, analysis, and triangulation points.

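### The Data analysis section lists implementation intensity, a post-randomisation variable, with baseline context as a covariate or stratum for the primary and secondary outcomes, so explanatory arm comparisons that use it are not randomised

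*Protocol article*

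**What the plan says.** The rule is in the Data analysis section of the protocol article. It opens with one list of contextual variables from process data, which starts with health system factors and gives every item the same role: "implementation intensity, site-level characteristics, and participant socio-demographic factors) will be operationalised as covariates or stratification variables in the quantitative analysis". The next sentence names the outcomes. Where appropriate, "multivariable regression models and subgroup analyses will be used to assess the influence of contextual factors on primary and secondary outcomes".

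Three other statements bear on how to read this.

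- The same section says that "The quantitative data will be analysed as part of the overall SHP trial statistical analysis plan". That plan is not shown.
- It describes the purpose as explanatory: "The analysis will aim to seek possible explanations for implementation and process outcomes achieved in the SHP trial".
- Under the heading on whether the study was implemented as planned, the article says "we will assess fidelity and dose (number of visits) of the trial procedures themselves". Dose is therefore something observed while the trial runs.

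The Process data collection section adds items recorded during follow-up, among them "any special diet taken by the women to improve their blood haemoglobin during, after pregnancy or details of treatment received during pregnancy or postpartum".

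**The concern.** The list joins two kinds of variable that need different treatment. A characteristic fixed before randomisation can be adjusted for, or used to form subgroups, without disturbing the balance that randomisation gives. A variable that arises afterwards and responds to the intervention cannot.

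Intensity fails on three counts. It is observed after randomisation. It depends on arm: Table 3 presents the planned strategies for the intervention arm, and the Quantitative data collection section places the health workers' app data at the intervention sites. It also reacts to how delivery is going: in Table 3, non-engagement prompts a site visit and support to health workers continues as needed, and the section on barriers and facilitators says monitoring leads to further strategies.

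Two errors can follow. Adjusting for intensity can remove the part of the effect that works through delivery. Comparing well-delivered intervention clusters with all control clusters sets a selected group against an unselected one. The article's Conclusion says the findings will guide adaptation and scale-up. A false message that the intervention works where it is well delivered would therefore matter.

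**Working it through.** No figure in the article corresponds to this point, so there is none to reproduce. The check sorts the variables and then sizes the two errors under stated assumptions.

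**Step 1. Which listed variables are post-randomisation?**

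| Variable | Timing |
|---|---|
| Health system factors | Either; not stated |
| Implementation intensity | After randomisation |
| Site-level characteristics | May be baseline |
| Participant socio-demographic factors | May be baseline |

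Only intensity is clearly post-randomisation.

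**Step 2. Splitting intervention clusters by intensity when there is no true effect.** The total of 3240 women is the required sample size in the Trial status section. Everything else is assumed:

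- 30 clusters per arm of 54 women (2 x 30 x 54 = 3240)
- 55% anaemia
- mean 6 visits, SD 1.5
- an unmeasured cluster quality that shifts anaemia by 3 to 8 percentage points per SD
- r-squared between quality and intensity of 0.25, 0.5 or 1.0

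With s the shift per SD and r the correlation, the expected contrast of either half with control has size

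sqrt(2/pi) x r x s = 0.798 x r x s.

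- Low end: 0.798 x 0.5 x 3 = 1.2 points
- High end: 0.798 x 1.0 x 8 = 6.4 points (simulated 6.2)
- Central, r-squared 0.5: simulated about -2.8 (high-intensity half) and +2.7 (low-intensity half). This corresponds to s = 2.8 / (0.798 x 0.707) = 5.0 points, inside the assumed range.

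The undivided arm difference stayed at about 0 throughout.

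**Step 3. Adjusting for intensity.** A second simulation used 60 clusters of 54 women, 50% control prevalence and 1000 runs per setting, all assumed. Intensity M varies in both arms and is raised by arm A:

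M = A + 0.7U + 0.7e

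Here U is an unmeasured cluster cause, and U and e have unit variance. The outcome is

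Y = constant + bM + uU + noise.

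The slope on M given A is b + u x 0.7/(0.49 + 0.49) = b + 0.714u. The total arm effect is b, so the adjusted arm coefficient is b - (b + 0.714u) = -0.714u.

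| Setting | Unadjusted, points (rejection) | Adjusted, points (rejection) | -0.714u |
|---|---|---|---|
| b = -9, u = 0 | -9.1 (82%) | 0.0 (5%) | 0 |
| b = 0, u = 0 | 0.0 (5%) | 0.1 (5%) | 0 |
| b = 0, u = -3 | -0.1 (5%) | +2.1 (12%) | +2.1 |
| b = 0, u = -6 | 0.0 (5%) | +4.3 (33%) | +4.3 |
| b = 0, u = -9 | 0.0 (5%) | +6.4 (54%) | +6.4 |
| b = -9, u = -6 | -9.0 (56%) | +4.3 (35%) | +4.3 |

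Positive values mean more anaemia in the intervention arm. With full mediation the effect vanishes. With a shared cause and no effect, a false one appears. With both, the sign reverses. With neither, there is no bias. The unadjusted column shows that leaving M out recovers the right answer each time.

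The 9-point effect reads the trial's 9% target as absolute, which the article does not state. The adjusted value does not contain b, so the relative reading (0.09 x 50 = 4.5 points here) would also go to 0 under full mediation.

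**The case against.** The strongest reply is that these are explanatory models. A reader might infer that the trial's treatment effect will itself be adjusted for intensity. The article does not say so. It takes effectiveness from the main trial's outcomes, gives these models the task of assessing context, and makes them conditional on being appropriate. That stands, and it limits the point to the explanatory comparisons.

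The second reply is that the unseen analysis plan may set this right, and that a covariate role also fits a model fitted within the intervention arm. Both are possible. But the article fixes a role for intensity, and it gives that role to baseline and delivery variables alike. This is a stated rule and not a detail left out.

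Two further inferences go beyond the text.

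- Diet and treatment received are recorded as process data, but the Data analysis section does not name them as covariates. They could enter only because its list is given as examples.
- Intensity is not defined, so it is not established that it exists only in the intervention arm. The Study design section says the evaluation includes both arms.

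A larger figure is also tempting. If intensity is coded 0 in control, regression under no effect gives an arm coefficient near +14 points. That is the slope times mean visits, 2.3 x 6 = 13.8: an extrapolation to an intervention cluster with zero visits. Centring intensity at the intervention-arm mean returns it to 0. It should not be set against the 9% target.

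**Conclusion.** The point holds for the explanatory analyses. The Data analysis section treats a post-randomisation delivery variable as if it were baseline context. Any arm comparison that conditions on it, or on other post-randomisation process data, loses the protection of randomisation. The documents do not show that the primary randomised comparison is affected, and site characteristics and socio-demographics are legitimate if measured before randomisation.

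Under the assumed inputs, the error is about 1 to 6 points for a median split with no true effect (central about 2.7), and complete loss of a 9-point effect when intensity carries all of it. These sizes rest on assumed cluster numbers, prevalence, visit counts and strength of the shared cause, and the upper end of the split range needs intensity to track cluster quality perfectly. Bias requires mediation through intensity or a shared cause. Both are plausible where delivery depends on the same health centres that provide care.

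**What to change.** Reword the paragraph in the Data analysis section, and the matching text in the analysis plan, to say two things.

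1. Between-arm models and subgroup analyses of the primary and secondary outcomes use only variables fixed before randomisation, such as state, health centre characteristics, baseline socio-demographics and baseline values. The influence of context is tested as an arm-by-baseline-variable interaction in the cluster-adjusted model.
2. Implementation intensity, dose, fidelity and other post-randomisation process variables are analysed separately. They are reported as associations within the intervention arm, with allowance for clustering and baseline adjustment, or by a formal causal method with its assumptions stated. These analyses are labelled exploratory and non-randomised.

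A blanket ban on intensity in any model containing arm would go too far. Formal mediation analysis needs both, and mechanisms of impact are a declared domain of the evaluation. An instrumental-variable analysis with arm as the instrument should be offered only if its exclusion assumption is stated and defended. That is difficult here, because the five components in Table 1 include education, supply support and stakeholder engagement, which can act outside measured visits.

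The cost is one paragraph of wording. The downside is that dose-response results carry a weaker, non-randomised label.

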## Methods

### Study setting

The study will be community-based and conducted in rural and semi-rural districts in India: Siddipet district in Telangana State and Jhajjar and Rohtak districts in Haryana State, India. Across India, the maternal mortality rate has significantly dropped in the last decades to an average 113 per 100 000 live births in 2018, according to estimates from the Sample Registration System (SRS).^
35
^ Recent estimates from the Health Management Information System (HMIS) indicate that maternal mortality in Telangana has dropped to 53 maternal deaths per 100,000 live births in 2017–2019^
35
^ and has been maintained at less than 70 in 2019–2021.^
36
^ In comparison, depending on estimates, Haryana had a higher maternal mortality rate of 101-91 for 2014–2018 (SRS) and 90 for 2017–2019 (HMIS), for 214 maternal deaths per 100 000 live births before 2018.^
37
^ As reported in the recent Comptroller and Auditor General of India’s Performance Audit, contrary to national rates, MMR in Haryana has increased from 98 (2015–2017) to 110 (2018–2020).^
38
^

The study will be conducted in both rural and semi-rural areas of India, specifically in the Siddipet district of Telangana and the Jhajjar and Rohtak districts of Haryana. These locations were strategically chosen to represent two distinct geographical, linguistic, and cultural populations. Each of the selected PHCs serves approximately 30,000 people across multiple villages. From each PHC’s catchment area, two villages will be selected to serve as the study sites for the trial. All community health workers and PHC staff from these sites will be eligible to participate in the study.

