### Participants

The participants for the qualitative components of this process and implementation evaluation, including focus group discussions (FGDs) and in-depth interviews (IDIs), will include a range of individuals involved in the SHP intervention. Both FGDs and IDIs are used to capture the perspectives of different stakeholders. FGDs will be conducted with ASHAs who participate in the training and are using the SHP app and diagnostic devices during their visits to explore both their shared and individual experiences in balancing their existing routine responsibilities and SHP activities, as well as their interactions with primary care doctors, auxiliary nurse midwives (ANMs), and women. IDIs will be conducted with women, primary care doctors, ANMs, health officials, women, and field supervisors in order to provide a space for participants to share sensitive details, personal reflections, and a secure environment to discuss their experiences (women). In addition, practical considerations around feasibility determined the mixed use of FGDs and interviews.

Sampling will be guided by thematic saturation, defined as the point at which no new themes or relevant insights emerge from successive interviews or FGDs. Based on the planned study design and practical feasibility, qualitative data collection will be conducted in 2 rounds (midline and endline), with an anticipated total of 32 IDIs and 12 FGDs across both field sites, as detailed in Table 3 (see below, under qualitative data collection plan). This will include 8 IDIs with pregnant and postpartum women, 8 IDIs with primary care doctors, 4 IDIs with ANMs, 8 IDIs with field supervisors, 4 IDIs with policy or health officials, and 12 FGDs with ASHAs. Final sample sizes may vary depending on achievement of thematic saturation.

Participants will be selected from those already involved in the SHP2 trial. Policy makers will be identified with the assistance of the district and state administrative heads. For healthcare workers, all healthcare workers who participated in the SHP study were eligible. For women, all participants of the study are eligible to participate, regardless of whether they have completed all assessments or not. In addition, women who have rejected participation are eligible. Participants who decline participation in the process evaluation are ineligible.

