Data collection was designed according to the objectives of the process evaluation. To understand how and why the SHP intervention may be effective, a relatively larger representation from healthcare providers is planned, as these are directly involved in using and delivering the SHP trial components. To understand for whom the implementation is useful, IDIs with women as the end beneficiaries will be conducted, and to gain in-depth accounts of their experiences. The number of IDIs and FGDs is also guided by feasibility. It is expected that in particular the interviews will provide a rich qualitative understanding and will complement the larger quantitative data of end beneficiaries conducted in the trial.

An iterative approach to data collection and analysis will be used until data saturation (i.e. when no new themes are emerging). Throughout the trial, the research team will regularly organise meetings with stakeholders and debriefing sessions with field supervisors to review emerging findings. If needed, additional interviews will be conducted.

An overview of the overall data collection plan for the SHP process evaluation is shown in Table 4.

**Table 4. table4-17455057261425789:** Overview of process evaluation data collection plan.

Stakeholders (intervention group)	*n* IDIs/FGDs in both fieldsites	*n* IDIs/FGDs in both fieldsites	
	Round 1: 12 months	Round 2: endline	Total *n* IDIs/FGDs
Women			
Pregnant and postpartum	4 IDIs	4 IDIs	8 IDIs
Healthcare providers			
ASHAs	6 FGDs	6 FGDs	12 FGDs
Primary care doctors	4 IDIs	4 IDIs	8 IDIs
ANMs	4 IDIs	0	4 IDIs
Project field team/managing the supply chain			
Field supervisors	4 IDIs	4 IDIs	8 IDIs
Policy officials			
Healthcare officials	0	4 IDIs	4 IDIs
Total intervention	16 IDIs and 6 FGDs	16 IDIs and 6 FGDs	32 IDIs and 12FGDs

ASHA: Accredited Social Health Activist; FGD: focus group discussion; IDI: in-depth interview; ANM: auxiliary nurse midwife.

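### MANOVA is named to assess differences in mechanisms, but it does not suit coded interviews and focus groups, and it understates p-values for cluster-level factors unless clustering is modelled

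*Protocol article*

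**What the plan says.** The qualitative analysis text in the Data analysis section states that "the findings from the CMO configurations will be analysed using thematic analysis using Atlas.ti", and continues with "descriptive statistics, and multivariate analysis of variance to assess differences in mechanisms". It does not say which mechanism variables form the response vector, which groups are compared, or what the unit of analysis is.

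Two kinds of data could enter. The section on contextual factors and mechanisms says: "Assumed mechanisms will be tested and refined through both quantitative data and qualitative insights from interviews and FGDs".

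- **Transcripts.** The Participants section plans "an anticipated total of 32 IDIs and 12 FGDs across both field sites", including "8 IDIs with pregnant and postpartum women, 8 IDIs with primary care doctors, 4 IDIs with ANMs, 8 IDIs with field supervisors", plus 4 interviews with officials; the focus groups are all with ASHAs. Table 4 plans these for the intervention group. The Data collection section describes the qualitative sample as purposive.
- **Quantitative measures.** The article lists app data, trial records, surveys and checklists. The design is cluster randomised. Of each PHC catchment, the Study setting section says "two villages will be selected to serve as the study sites for the trial".

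The Data analysis section also sends the quantitative data to the overall trial SAP. It mentions multivariable regression where appropriate, but for the influence of context on primary and secondary outcomes, not for mechanisms.

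**The concern.** MANOVA compares mean vectors between groups. It relies on independent units and on responses that are continuous and approximately jointly normal.

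Coded transcripts do not supply that. A theme is in essence present or absent in a transcript, and a focus-group code describes the group rather than a person. The sample was also chosen for variety, not drawn at random, so a p-value has no clear population to refer to.

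Quantitative measures on women, ASHAs or doctors come closer to continuous responses, but these people share villages and PHCs. A test that treats them as independent overstates the information about any factor that varies only between clusters, such as site characteristics or state.

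Explaining how context and mechanisms shaped the outcomes is one of the evaluation's stated objectives, and the Conclusion expects the results to guide scale-up. Ordinary site-to-site variation could be reported as an established difference in mechanism.

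**Working it through.** **1. The plan's own counts.** From Table 4, interviews are 8 women + 8 doctors + 4 nurse midwives + 8 field supervisors + 4 officials = 32. Focus groups are 6 + 6 = 12. Both match the stated totals, and there are 44 transcripts in all.

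**2. When MANOVA can be computed on transcripts.** The error matrix is invertible only if the number of responses p does not exceed the residual degrees of freedom, N − g, for N units in g groups.

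| Comparison | N | g | Largest p |
|---|---|---|---|
| All transcripts by stakeholder group | 44 | 6 | 38 |
| Interviews by stakeholder group | 32 | 5 | 27 |
| ASHA focus groups by state | 12 | 2 | 10 |
| Women by state | 8 | 2 | 6 |
| Nurse midwives, or officials, by state | 4 | 2 | 2 |

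The article names no comparison groups, so these splits are illustrations. The test is computable when transcripts are pooled and breaks down only within small groups with several codes. With simulated independent normal data it kept its level (n = 8, p = 3: 5.9%; n = 44, p = 5: 5.3%). The objection to pooled use is therefore the nature of the data, not the arithmetic.

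**3. Type I error on clustered measures.** The article gives neither the intracluster correlation (ICC) nor the cluster size m, so both are assumed. For a factor that varies only between clusters, the naive test statistic is inflated by about

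DEFF = 1 + (m − 1) × ICC.

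With 4 responses and a nominal 5% level, the critical value of chi-square on 4 df is 9.488, and the true type I error is about P(chi-square on 4 df > 9.488 / DEFF).

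| m | ICC | DEFF | 9.488 / DEFF | Type I error |
|---|---|---|---|---|
| 27 | 0.01 | 1.26 | 7.53 | 11% |
| 27 | 0.03 | 1.78 | 5.33 | 26% |
| 27 | 0.05 | 2.30 | 4.13 | 39% |
| 54 | 0.01 | 1.53 | 6.20 | 18% |
| 54 | 0.03 | 2.59 | 3.66 | 45% |
| 54 | 0.05 | 3.65 | 2.60 | 63% |

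Simulation of the two-group test with 4 responses (600 runs per scenario) gave 12%, 24% and 39% for m = 27, and 16%, 47% and 61% for m = 54.

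A second simulation used 3 responses, the required 3240 women and 1000 runs per scenario. With 120 clusters of 27 it gave 11% at ICC 0.01 and 33% at ICC 0.05. With 60 clusters of 54 it gave 16% and 54%. At ICC 0 it stayed at about 5%.

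**4. Where the inflation does not follow.** These figures are for cluster-level factors. They do not carry over to factors that vary within clusters, such as a woman's own socio-demographic characteristics.

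**The case against.** The strongest reply has four parts.

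- **The SAP may deal with it.** The article defers quantitative analysis to the trial SAP, where clustering may be handled. That stands: the missing clustering term is not in itself a fault of the article. But MANOVA is a method the article positively names, in the text on qualitative and CMO analysis, and a clustering provision elsewhere would not make it suitable for theme codes.
- **Other data could suit it better.** Survey scores, checklists and the sustainability tool could supply numerical responses to compare across stakeholder groups. This is fair. Many of those respondents also work or live within shared PHCs, however, so independence is still in doubt. That theme codes are presence or absence is likewise an inference from the description of coding and theme frequency, not something the article states.
- **The sizes rest on assumptions.** This is correct for the ICC, the cluster size and the number of responses.
- **The analysis is exploratory.** MANOVA is one of three tools in one sentence, with no significance rule attached, and the section's stated aim is to seek possible explanations. This stands and limits the severity.

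A reader might go further and infer that MANOVA cannot be computed on these data at all, or that every p-value for mechanisms will be far too small. The documents support neither. Computability depends on an unstated number of responses and on unstated groups. The inflation depends on an unstated ICC and cluster size and applies to cluster-level factors only.

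**Conclusion.** The point holds in a limited form. MANOVA is a poor choice for the coded interviews and focus groups: pooled, it yields a number without a valid interpretation, and within groups of 8 or 4 split by state it is confined to at most 6 or 2 responses. For quantitative mechanism measures compared across cluster-level factors, an unadjusted MANOVA would have a type I error of about 11% to 63% rather than 5%, assuming ICCs of 0.01 to 0.05, 27 to 54 women per cluster and 4 responses. Even the mildest of these cases doubles the nominal level. Factors varying within clusters are not covered by that range, and the SAP may already model clustering. The trial's primary outcome is not affected. The wording should be fixed, but it does not threaten the trial's main result.

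**What to change.** In the Data analysis section:

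1. Delete MANOVA.
2. State that coded interview and focus-group findings will be compared descriptively, in CMO matrices of stakeholder group by site, without significance tests.
3. For quantitative mechanism measures, name the measures, the groups compared and the unit of analysis. Use mixed models or GEE with PHC as the clustering unit, add a small-sample correction if clusters are few, and cross-refer to the trial SAP. A multiplicity adjustment is optional in an exploratory analysis.

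The cost is a change of wording and standard software. The downside is wider intervals and fewer nominally significant differences in mechanism.
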